# A cluster randomized controlled trial comparing Virtual Learning Collaborative and Technical Assistance strategies to implement an early palliative care program for patients with advanced cancer and their caregivers: a study protocol

**DOI:** 10.1186/s13012-021-01086-3

**Published:** 2021-03-11

**Keywords:** Implementation strategies, Implementation science, Early palliative care, Advanced cancer, Cluster-randomized controlled trial

## Abstract

**Background:**

Virtual Learning Collaboratives (VLC), learning communities focused on a common purpose, are used frequently in healthcare settings to implement best practices. Yet, there is limited research testing the effectiveness of this approach compared to other implementation strategies. This study evaluates the effectiveness of a VLC compared to Technical Assistance (TA) among community oncology practices implementing ENABLE (Educate, Nurture, Advise, Before Life Ends), an evidence-based, early palliative care telehealth, psycho-educational intervention for patients with newly diagnosed advanced cancer and their caregivers.

**Methods:**

Using Reach, Effectiveness, Adoption, Implementation, Maintenance (RE-AIM) and Proctor’s Implementation Outcomes Frameworks, this two-arm hybrid type-III cluster-randomized controlled trial (RCT) will compare two implementation strategies, VLC versus TA, among the 48 National Cancer Institute Community Oncology Research Program (NCORP) practice clusters that have not historically provided palliative care to all patients with advanced cancer. Three cohorts of practice clusters will be randomized to the study arms. Each practice cluster will recruit 15–27 patients and a family caregiver to participate in ENABLE. The primary study outcome is ENABLE uptake (patient level), i.e., the proportion of eligible patients who complete the ENABLE program (receive a palliative care assessment and complete the six ENABLE sessions over 12 weeks). The secondary outcome is overall program implementation (practice cluster level), as measured by the General Organizational Index at baseline, 6, and 12 months. Exploratory aims assess patient and caregiver mood and quality of life outcomes at baseline, 12, and 24 weeks. Practice cluster randomization will seek to keep the proportion of rural practices, practice sizes, and minority patients seen within each practice balanced across the two study arms.

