### Primary aim (implementation outcome, patient level)

Compare the effectiveness of VLC vs. TA on ENABLE program uptake, as measured by the proportion of patients who complete the ENABLE program (i.e., have a palliative care assessment and complete the six ENABLE sessions). *Hypothesis*: Practice clusters randomized to VLC will have greater ENABLE program uptake than practice clusters randomized to TA.

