##### Patient inclusion criteria

Patients must be diagnosed with advanced cancer (stage III/IV, recurrence, or progressive solid tumor cancer) within the last 90 days and have an expected survival of at least 6 months. Patients must be English-speaking, at least 18 years old, willing to complete the palliative care assessment and ENABLE sessions, have access to a telephone that can receive calls, and able to provide informed consent to participate in the study.

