***Aim 2 Outcome (Service Outcome, Practice Level)***				
Overall Program Implementation	ENABLE GOI	Baseline, 6, 12 months	Coordinator and Nurse Coach (other staff may attend call)	The ENABLE General Organizational Index (GOI) is conducted via a phone interview with the Coordinator and Nurse Coach (other staff may attend call) to assess factors that influence institutional implementation and fidelity to an evidence-based practice. It covers 12 domains and is scored on a Likert scale. Qualitative analysis will also be conducted [38–40].
*Additional Implementation Outcomes*				
ENABLE Program Implementation	ENABLE RE-AIM Self-Assessment Tool	Baseline, 6, 12 months	Coordinator and Nurse Coach	The ENABLE RE-AIM Self Assessment Tool (Reach, Efficiency, Adoption, Implementation, and Maintenance) was developed in our prior work to collect reach, adoption, implementation, and maintenance [23, 24, 38]. *Reach* is defined as the number of enrolled participants divided by the number of eligible participants. *Efficacy* will be measured by patient and caregiver quality of life and mood outcomes (see Explanatory Aim 1 measures). *Adoption* will be measured by calculating the number of oncology physicians who refer patients divided by those who have the opportunity to refer patients to the study. *Implementation* is captured in the study’s primary outcome, ENABLE uptake. *Maintenance* will be measured by the presence of the ENABLE program 6 months after the completion of the VLC or TA implementation strategy in the ENABLE Sustainment Survey. The ENABLE Nurse Coach and/or coordinator will complete the online ENABLE RE-AIM Self-Assessment tool at baseline, 6 months (± 8 weeks), and 1 year (± 8 weeks).
Perceptions of Early Palliative Care	Provider Perceptions of Early Palliative Care Survey	Baseline, 15 months	Oncologist and Nurse Coach	The survey asks about attitudes about palliative care, feelings about palliative care specialists, comfort with an preferences for providing early concurrent oncology palliative care, and description of early concurrent palliative care provided in the practice cluster [38, 41]. Responses are on a Likert scale.
*VLC and TA Process Outcomes*				

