### Statistical analysis

All randomized practice clusters will be included in primary comparisons, according to their group assignment, and regardless of their degree of participation in the study. Primary data analysis will include descriptive statistics for baseline practice cluster characteristics, patient characteristics, and outcomes in each RCT arm. We will examine the balance between RCT arms with respect to baseline characteristics (e.g., age, sex, race, cancer type, stage) using effect sizes, such Cohen’s d and Cramer’s. Factors showing non-trivial imbalances between comparators will be used as adjusting covariates in the between-group comparisons. Analysis will be conducted using the latest versions of SAS and R.

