Like most research, we have encountered challenges during the study start-up period. First, the COVID-19 pandemic significantly impacted the ability for NCORP practices to conduct research and resulted in a need to rely on telehealth. Although most ENABLE activities were already offered via telephone, we modified the protocol so that all study procedures can now be conducted remotely, including the consent process and the comprehensive palliative care assessment. During this time, NCORP practices also expressed concern about the time required to complete the Nurse Coach training. To reduce training burden, the length of the web-based ENABLE Nurse Coach training was reduced from 25 h to approximately 19 h. We anticipate the reduced number of training hours may be beneficial beyond the study given our goal to make the ENABLE training more broadly scalable to nurses and advanced practice providers interested in implementing this EPC program. We also amended the originally required cohort size (*n* = 16) and will permit cohorts of 8–20 practice clusters (4–10 per study arm). To account for this in analyses, we will assess for confounding by cohort. Lastly, although each practice cluster will be expected to deliver ENABLE to 15–27 patients, we recognize that may not happen. To account for this, we will include an option to recruit additional practice clusters (up to 20% of 48 which is 58 practices) and additional cohorts. Despite these challenges, we anticipate the first cohort will launch in the first half of 2021.

There are several anticipated lessons learned from this study. First, to the best of our knowledge, this is the first large-scale study measuring the implementation of early palliative care in community-based oncology practices. To measure implementation, we developed and refined palliative care implementation measures and anticipate that lessons learned will be used to improve these measures. Second, this study not only seeks to identify the superior implementation strategy (VLC or TA), but also to examine the key components of each strategy. To do so, we have developed measures of participation, engagement, and fidelity that have not been applied in other published literature. Lessons learned will inform refinement of the measures and advance the field.

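### The primary outcome is announced over eligible patients and all randomised practices, but it is sized and modelled on enrolled, assessable patients, so it measures completion after enrolment, not uptake in the eligible population

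*Protocol article*

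**What the plan says.** The Methods part of the abstract defines the outcome by its denominator: "The primary study outcome is ENABLE uptake (patient level), i.e., the proportion of eligible patients who complete the ENABLE program". The Primary aim section is less specific and gives uptake "as measured by the proportion of patients who complete the ENABLE program".

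The Sample size section starts from enrolled patients, removes 20% whose completion cannot be assessed because of death or illness, and counts 12 of 15 per practice. The aim 1 analysis is a logit GEE with one record per patient. It scores completion against the 12-week assessment, and its supplemental analyses concern recruited patients.

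On the analysis set, the Statistical analysis section says: "All randomized practice clusters will be included in primary comparisons, according to their group assignment, and regardless of their degree of participation in the study".

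Table 2 (RE-AIM Self-Assessment Tool) holds the enrolment step apart. Reach "is defined as the number of enrolled participants divided by the number of eligible participants", while the implementation component of RE-AIM is assigned to the primary outcome. On the target of 15–27 patients per practice, the Discussion says "we recognize that may not happen" and provides for additional practices and cohorts.

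**The concern.** There are two internal conflicts. First, the abstract's denominator (eligible) is not the one used for sizing and modelling (enrolled and assessable), and the protocol itself distinguishes these populations by defining Reach as their ratio. Second, the inclusion promise covers all randomised practices, but the stated model has no record for a practice without an analysable patient.

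They matter because of when enrolment happens. Under Randomization, arms are assigned after training and practices know their arm and the hypotheses. Practice staff then identify and approach patients, and referral and enrolment are reviewed in both the VLC sessions and the TA calls. Patients must also be "willing to complete the palliative care assessment and ENABLE sessions". Enrolment is therefore a step after randomisation that the strategies may influence. A comparison of completion among those who enrolled is conditional on it. The trial intends to conclude which strategy better implements ENABLE, and a practice that enrols few or none of its eligible patients has an implementation problem that this outcome does not register.

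**Working it through.** **Which patients does the plan's own figure count?** Inputs from Sample size: 24 practices per arm, 12 assessable patients each, ICC 0.05, alpha 0.01 (taken as two-sided), power 80%, reference proportion 0.52.

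- Patients per practice: 15 × (1 − 0.20) = 12. Per arm: 24 × 12 = 288.
- Design effect: 1 + (12 − 1) × 0.05 = 1.55. Effective size: 288 / 1.55 = 185.8 per arm.
- Detectable difference (two-sided, unpooled z): 0.171, giving OR 2.06 and RR 1.33, which match the stated OR and RR. A noncentral t with 46 degrees of freedom gives 0.177, which rounds to the stated 0.18.

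The figure is reproduced using enrolled, assessable patients, with 12 from every one of the 48 practices. The working denominator is therefore not the eligible population.

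**How the two quantities relate.** Leaving unassessable patients aside, uptake among eligible patients = Reach × completion among enrolled. The document gives no reach values, so every reach below is an assumption chosen to show the range.

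| Reach TA / VLC | Completion TA / VLC | Difference among enrolled | Difference among eligible |
|---|---|---|---|
| 0.50 / 0.50 | 0.52 / 0.70 | +0.18 | 0.350 − 0.260 = +0.090 |
| 0.30 / 0.60 | 0.52 / 0.52 | 0.00 | 0.312 − 0.156 = +0.156 |
| 0.60 / 0.40 | 0.52 / 0.70 | +0.18 | 0.280 − 0.312 = −0.032 |

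With equal reach the two measures agree in direction. They separate only when reach differs between arms.

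**Practices without patients (also assumed).** Suppose 4 of 24 VLC practices enrol nobody, the others complete at 0.70, and TA completes at 0.52. The model still sees 0.70 − 0.52 = +0.18. Counting the empty practices as zero in an unweighted practice mean gives 20/24 × 0.70 = 0.583, a difference of +0.063. The number of empty practices that would remove the whole difference is 24 × (1 − 0.52/0.70) = 6.2. This practice mean is not the planned GEE estimate.

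**Power.** At a difference of 0.18 (pooled z), power is 0.84 with 24 contributing practices per arm, 0.80 with 22, 0.75 with 20 and 0.70 with 18. Losing a couple of practices per arm costs little. The problem is what is being estimated, not precision.

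**The case against.** The strongest reply is that the conflict over the denominator is one word in an abstract. The abstract itself says that each practice will recruit 15–27 patients, and the body makes the enrolled denominator recoverable. That stands, and it is why the remedy for the first conflict is a correction of wording.

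Second, separating enrolment from completion looks deliberate, since Reach is a named additional outcome collected at baseline, 6 and 12 months. This is a genuine partial mitigation. However, the article describes no between-arm analysis of Reach and does not bring it together with uptake.

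Third, the Discussion foresees under-recruitment, not practices with no patients. Practices must have physicians willing to enrol, and they are randomised only after training. This also stands: empty practices are possible but not predicted. The inclusion sentence can be read as ordinary intention-to-treat wording, yet it extends to any degree of participation, which the model cannot guarantee.

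Fourth, some protection against differential recruitment exists: adjustment for non-trivial baseline imbalances, patients unaware of their practice's arm, and a supplemental analysis of sessions completed among all recruited patients. None of these reaches eligible patients who were not enrolled.

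Finally, completers over eligible is itself imperfect. If the 15–27 target acts as a quota, a practice with an assumed 200 eligible patients could not exceed 27/200 = 13.5%, whatever its strategy achieved. The ratio also mixes refusal of research consent with programme uptake. Both are reasons to keep that analysis supportive.

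**Conclusion.** The two statements need correcting, and the primary conclusion needs a stated limit: it is about completion among enrolled, assessable patients. The conflicts rest on the text alone. That enrolment follows randomisation is read from the Randomization, VLC and TA sections, because the design figure is not shown.

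The size of any gap between the two measures cannot be determined from the document. A reader might infer that the planned analysis would probably point to the wrong strategy, or that the primary outcome must be replaced by one that counts every unenrolled patient or empty practice as a failure. The document supports neither. Reversal of sign appears only under reach values assumed for illustration, and completion among enrolled patients is a legitimate outcome provided that it is named as such. Nor does the document support treating the eligible-patient ratio as a second result that must share in wording the primary conclusion, given the cap created by the enrolment target.

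**What to change.** 1. In the abstract, replace eligible with enrolled in the outcome definition.
2. In Statistical analysis, say that all randomised practices with at least one analysable patient enter the primary model, as assigned.
3. Limit the primary conclusion to completion among enrolled patients.
4. Pre-specify a supportive practice-level comparison between arms of Reach and of completers divided by eligible patients. Cover all randomised practices, enter non-enrolling practices as 0, and account for cohort.

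The primary model and sample size stay as they are. The cost is wording plus one supportive analysis of counts already collected for Reach and in the contact log. It should be fixed before outcome data are seen.

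There are two downsides to state with the analysis: eligible counts are self-reported by practices, and the 15–27 target can cap the ratio at large practices. One practical point also needs settling. The Reach tool is completed at baseline, 6 and 12 months, while the contact log covers months 1–15, so numerator and denominator must be taken over the same period.

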**Discussion:**

This study will advance the field of implementation science by evaluating VLC effectiveness, a commonly used but understudied, implementation strategy. The study will advance the field of palliative care by building the capacity and infrastructure to implement an early palliative care program in community oncology practices.

**Trial registration:**

Clinicaltrials.gov. NCT04062552; Pre-results. Registered: August 20, 2019. https://clinicaltrials.gov/ct2/show/NCT04062552?term=NCT04062552&draw=2&rank=1

Contributions to the literature
As recommended by oncology professional organizations, this study will promote the use of an evidence-based, telehealth, early palliative care program for patients with advanced cancer among a national sample of community oncology practices.Improve understanding of effectiveness of two commonly used implementation strategies, the Virtual Learning Collaborative (VLC) and Technical Assistance (TA).Evaluates measures of ENABLE implementation, organizational factors that influence fidelity to implementation, and patient and caregiver outcomes.Lessons learned will inform measurement of multi-level implementation outcomes related to early palliative care interventions.Lessons learned will inform future use of telehealth interventions and virtual implementation strategies.

## Introduction

### Background and rationale

Due to the benefits of early palliative care (EPC) in randomized controlled trials [1–3], the American Society of Clinical Oncology recommends “ … combined standard oncology care and palliative care … early in the course of illness for any patient with metastatic cancer and/or high symptom burden” [4] (p.881). Yet, the National Cancer Institute (NCI)’s “Landscape Study” revealed that only 30% of community oncology practices have access to palliative care multidisciplinary teams in outpatient settings [5, 6]. Even practices offering EPC are often unable to meet the needs of all advanced cancer patients due to a limited palliative care workforce and the large number of patients with advanced cancer and caregivers [7, 8]. Training existing oncology staff to provide evidence-based palliative care interventions [9] is a potentially scalable and sustainable approach to address the national shortage of palliative care specialists. The ENABLE (Educate, Nurture, Advise, Before Life Ends) program is an example of such an intervention that can be implemented by healthcare organizations seeking to develop or enhance palliative care services.

ENABLE is an evidence-based, scalable model of EPC promoted by the National Cancer Institute Evidence-Based Cancer Control Programs (EBCCP), formerly known as Research-Tested Intervention Program (RTIP) [10–12]. ENABLE is led by a Nurse Coach and includes a comprehensive palliative care assessment, weekly telehealth coaching sessions (6 for patient; 3 for caregiver) using the Charting Your Course© guidebook. The coaching sessions review essential palliative care topics, such as problem solving, coping, symptom management, self-care, communication, decision-making, and advance care planning and monthly follow-up calls (Fig. 1). The parallel ENABLE program topics for caregivers mirror the patient sessions. ENABLE has not been widely used in community oncology practices despite being publicly available through the EBCCP. An effective implementation strategy to address implementation barriers (e.g., lack of knowledge about evidence-based EPC, insufficient infrastructure) is needed to equip oncology practices to develop the skills to implement and sustain ENABLE. However, it is unclear which strategy would be most successful in assisting implementation.

**Fig. 1 Fig1:**
[figure not shown]
Charting your course (CYC) chapter/session topics

Two common strategies to enhance implementation of evidence-based practices include VLC and TA. VLC is an innovative version of the traditional (face-to-face) Learning Collaborative, developed by the Institute for Healthcare Improvement (IHI) to guide clinical teams in implementing evidence-based practices [13]. Learning collaboratives use group interaction among teams to guide clinical improvement efforts. VLC, which uses a virtual (web-based) platform instead of face-to-face meetings, was designed to decrease the cost of participation and increase the speed of incorporating lessons into practice [14, 15]. The evidence on VLCs appears to improve processes, but is inconclusive on outcomes [16, 17].

The second strategy, TA, is defined as “interactive support that is individualized to the specific needs of individuals or teams.” (p.3) [18]. TA is typically provided one-on-one to a single organization and does not use a community structure to encourage shared learning or collaboration [19]. The evidence on TA effectiveness is minimal [19, 20]. To our knowledge, there are few rigorous trials comparing the effectiveness of VLC or TA and more testing with rigorous study design is needed [14, 15, 21, 22]. Which strategy would be most effective for the widespread implementation of ENABLE in community oncology practices is unclear.

To address these gaps in implementation science and palliative care, we developed a cluster randomized controlled trial (RCT) that compares VLC to TA for implementing ENABLE in community oncology practices. Our primary hypothesis is that practices randomized to VLC will outperform those randomized to TA resulting in a higher proportion of patients completing the ENABLE program. The more effective implementation of ENABLE will be due to the benefits of group dynamics (e.g., shared experiences, accountability, learning, discussion, and interactions), and quality improvement learning/skills that occur in the VLC but not in TA. Ultimately, a greater uptake of ENABLE will lead to better outcomes (mood and quality of life) for the patients and caregivers at the practices exposed to VLC compared to those exposed to TA.

### Study aims and hypotheses

Based on Proctor’s implementation framework, the purpose of this two-arm hybrid type-III cluster RCT in community oncology practices is to compare the effectiveness of two strategies, VLC and TA for implementing the evidence-based ENABLE program (Fig. 2).

**Fig. 2 Fig2:**
[figure not shown]
Adapted proctor’s implementation outcomes model applied to study aims

### Primary aim (implementation outcome, patient level)

Compare the effectiveness of VLC vs. TA on ENABLE program uptake, as measured by the proportion of patients who complete the ENABLE program (i.e., have a palliative care assessment and complete the six ENABLE sessions). *Hypothesis*: Practice clusters randomized to VLC will have greater ENABLE program uptake than practice clusters randomized to TA.

